## Abstract

**Trial registration::**

This study protocol was registered in Research Registry (researchregistry6202).

## Introduction

1

Chronic kidney disease (CKD) is defined through the National Institute of Diabetes and Digestive and Kidney Diseases.^[1,2]^ It refers to the continuous decline of renal function with the rate of glomerular filtration below 60 mL/min.^[3]^ This disease affects 8% to 16% of the world's population and it is generally ignored by clinicians and patients. CKD is more common in the low-income and middle-income countries than in the high-income countries.^[4]^ Globally, the most familiar causes of CKD are hypertension and diabetes, but there are some other causes, for instance, infections, glomerulonephritis, and the environmental exposures (e.g., pesticides, herbal medicines, and air pollution).^[5–7]^ Since 2007, the global CKD prevalence has increased by 34.2%. In 2017, CKD led to 123 million deaths.^[8]^

Peritoneal dialysis (PD) is a kind of effective treatment of renal replacement for the CKD patients.^[9,10]^ The outcomes of PD treatment leads to the removal of excess waste and fluid from the blood into dialysate and offers better health results in terms of life quality and survival rate in CKD patients. Due to the advantages of simple operation and high cost-effectiveness, PD is extensively utilized in many countries. At present, >270,000 patients worldwide are treated with PD, accounting for approximately 10% of all the dialysis patients.^[11]^ In addition, the annual percentage of patients undergoing PD worldwide has enhanced by 8%, higher than the percentage of hemodialysis.^[12]^

The CKD patients may have a variety of complications, for instance, catheter dysfunction, infection, malnutrition, and fatigue. The malnutrition in CKD patients is related to their lower life quality, higher hospitalization rates, and higher risk of cardiovascular disease, as well as the increased morbidity and mortality. Hence, it is very important to monitor and then manage the nutritional status of CKD patients receiving PD. Thus, we perform this randomized controlled study protocol to introduce a continuing nursing program based on Omaha system (OS) for the patients with CKD receiving PD treatment.

## Methods

2

The experiment will be implemented from November 2020 to May 2021 at Wuhan No.1 Hospital. The experiment was granted through the Research Ethics Committee of Wuhan No.1 Hospital (2020003281) and recorded in research registry (researchregistry6202). Prior to registration, the patients who are recruited receive written informed consent.

### Inclusion criteria and exclusion criteria

2.1

Patients who meet the following criteria will be selected: voluntary participation, aged 20 to 60; undergoing the regular PD treatment for at least 3 months. Patients will be excluded if the patients are in unstable status, or experience the intermittent PD or some other kinds of dialysis mode, have severe cachexia, infection or malnutrition, or if they have mental disorders.

### Randomization

2.2

Two patients meet inclusion criteria and exclusion criteria are included. In the random envelope, a random number is assigned to whole patients through the random-number table, and the distribution result is invisible. Patients are assigned randomly to conservative group (n = 100) and surgical group (n = 100).

### Intervention

2.3

In control group, patients are given routine treatment, containing general guidance associated with PD and the outpatient telephone calls from the clinical nurses during follow-up. In study group, the patients are given the continuous nursing treatment scheme based on OS as shown below. Education: the self-management health lecture of PD are held, mainly including the knowledge of environment preparation and PD operation, involving the process of PD operation, the dialysate heating approach, aseptic operation technology, the times of perfusion and dialysis drainage, the complications related to PD, and the PD tube skin care. In the aspect of dietary management information, low-phosphorus diet, low-salt diet, high-quality protein diet, the food kinds and importance of the intake of potassium are the major contents. After finishing the lecture, a group discussion is organized to in-depth investigate the health problems raised by the patients. The materials of health education are publicized in Wechat group twice a week. And the materials focus on nutrition management and PD. Moreover, the video for the process of PD operation is made and played in Wechat group to help the patients understand the operation process. Procedure and treatments: firstly, the self-designed evaluation table based on Omaha Question Classification System is utilized to identify the nursing problems of patients, involving cognitive, nutrition, emotional, and the economic problems. Afterwards, the objectives of nursing intervention are established and the intervention strategies are conducted (for instance, personalized health education, guidance, or consultation). Case management: the patients are instructed on how to record their own diet in their self-management manual, involving the quantities and types of daily diet. According to the dietary records, clinical nutritionists make dietary suggestions, and then formulate the target diet. Surveillance: in the process of Wechat, outpatient, and telephone follow-up, the weight, the management of drug, patient's diet, sleep, working conditions as well as some other factors are assessed to determine the unsatisfied nursing needs of patients and carry out targeted intervention.

### Clinical endpoints

2.4

The clinical results are the biochemical parameters, anthropometry, as well as the subjective global assessment after intervention.

### Statistical analysis

2.5

All the data can be recorded into the software of Microsoft Excel 2010, and the data are analyzed through utilizing the software of IBM SPSS Statistics for Windows, version 20 (IBM Corp., Armonk, NY). Subsequently, all data are represented via the proper characteristics, for instance, median, mean, and percentage. The categorical variables and continuous variables are respectively analyzed using independent *t* tests and chi-squared-tests. *P* value <.05 indicates that there is statistical significance.

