## Results

3

Table 1 indicates the clinical outcomes between 2 groups.

**Table 1 T1:** The clinical endpoints between the two groups.

Variables	Study group (n = 100)	Control group (n = 100)	*P* value
Well nourished			
Moderately malnourished			
Severely malnourished			
Body mass index			
Triceps skin-fold thickness			
Mid-arm muscle circumference			
Handgrip strength			
Hemoglobin			
Albumin			
Total cholesterol			

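### Section 2.5 reverses the tests: t tests for categorical and chi-squared tests for continuous variables; for the seven continuous outcomes that test would miss most or all of a group difference

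*Protocol article*

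**What the plan says.** The Statistical analysis section (2.5) of the protocol article contains one sentence that assigns tests to data: "The categorical variables and continuous variables are respectively analyzed using independent *t* tests and chi-squared-tests". It also sets a 0.05 significance threshold. It names no other test.

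The Clinical endpoints section (2.4) lists what is to be compared: "The clinical results are the biochemical parameters, anthropometry, as well as the subjective global assessment after intervention". Table 1 in the Results section (3) sets these out in ten rows with a single P-value column:

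- Three rows are the levels of one ordered categorical variable, nutritional status, and include "Moderately malnourished" and "Severely malnourished".
- Seven rows are continuous measurements: body mass index, "Triceps skin-fold thickness", "Mid-arm muscle circumference", handgrip strength, hemoglobin, albumin and total cholesterol.

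The Randomization section (2.2) and Table 1 both give 100 patients per group.

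**The concern.** Because of *respectively*, the sentence has only one grammatical reading: categorical variables go to the independent t test and continuous variables to chi-squared. The usual pairing is the opposite.

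A chi-squared test on raw continuous data makes each distinct recorded value its own category. It takes no account of whether one value is larger than another, so a shift of the whole distribution in one group hardly registers. A t test on a three-level category can only be run after numbers have been attached to the levels, and the article does not say which numbers.

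This is the only inferential rule in the article. An analyst who follows it gets nearly uninformative P values for seven of eight outcomes. An analyst who applies the conventional pairing departs from the published plan without a record of having done so.

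**Working it through.** The article gives no sample-size or power figure, so there is nothing of its own to reproduce. The check asks what the written rule does to each kind of row.

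**Inputs from the article:** 100 per group; significance at 0.05 (sidedness not stated, two-sided assumed); seven continuous outcomes and one three-level outcome.

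**Inputs assumed, because the article gives none:** a continuous outcome with mean 36 and SD 4; a true shift of 0 or 0.5 SD; recording to 0.1 or to whole units; category shares of 60/30/10%.

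**1. Continuous outcome, all 200 values distinct.** The table is 2 × 200. With equal groups, a value seen *x* times in one group and *y* times in the other contributes (x − y)² / (x + y) to the Pearson statistic. Each value occurs once, so each contributes 1 and the statistic is 200. The degrees of freedom are (2 − 1)(200 − 1) = 199, and P = 0.467. Nothing here depends on which group holds the larger values: data with no shift and data with a 3 SD shift give the same P. The expected count in every cell is 0.5.

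**2. Continuous outcome with ties from rounding (simulation).**

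| Recording | True shift | Chi-squared rejects | t test rejects |
|---|---|---|---|
| to 0.1 | 0 | about 0.1% | 5–6% |
| to 0.1 | 0.5 SD | about 1% or less | about 94% |
| whole units | 0 | about 3% | 5–6% |
| whole units | 0.5 SD | 33–34% | 93–94% |

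The t-test power can be confirmed by formula: 0.5 / √(2/100) = 3.54; 3.54 − 1.96 = 1.58; Φ(1.58) ≈ 0.94.

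The damage depends on rounding. With values to 0.1, essentially every expected count is below 5. With whole units, a little over half are, and the most common value is expected about 20 times in 200 patients, or about 10 per arm.

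**3. Nutritional status, one level coded 0/1.** With no true difference, the type I error is 0.044–0.052 for both the t test and chi-squared. Over all scenarios tried, the two tests reach different decisions in under 1% of runs.

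**4. Nutritional status, levels scored 1-2-3.** The t test's type I error is about 0.054, close to nominal. It compares mean scores only. Take shares of 60/30/10 against 70/10/20. The means are 0.6 + 2 × 0.3 + 3 × 0.1 = 1.5 and 0.7 + 2 × 0.1 + 3 × 0.2 = 1.5. The t test rejects in 4.8% of runs and chi-squared in about 94%. For an orderly improvement, 60/30/10 against 75/20/5, the t test does no worse (62% against 54%).

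**The case against.** The strongest reply is that this is a slip of word order. Both conventional tests are named, only their order is wrong, and the article's English is loose elsewhere. The preceding sentence, on describing data by median, mean or percentage as appropriate, fits ordinary handling by variable type. A competent analyst would probably swap the tests without comment. That is likely true, and it makes the harm conditional on someone following the sentence literally. It does not make the printed rule right. Nor does an analysis plan that is not shown: if that plan has the correct pairing, the article contradicts it.

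A reader might infer that every row of Table 1 would receive an invalid test. The calculations do not support that. For the nutritional-status rows the t test is the wrong choice and its coding is unspecified, but its type I error stays close to nominal, and with 0/1 coding it nearly matches chi-squared.

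A reader might also take near-empty tables, with expected counts of about 0.5 to 1 per cell, as given. That holds only if nearly all values are distinct, and the article states no SDs, units or recording precision. Under whole-unit recording the tables are fuller and the loss of power is smaller, though still severe.

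Finally, the article does not name a mean difference as its target of estimation, so the case rests on the mismatch between test and data type, not on a failure to estimate a stated quantity.

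**Conclusion.** The point holds in this form: the test assignment in section 2.5 is reversed, probably by a slip, and no other part of the article corrects it.

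Its full force falls on seven of the eight outcomes. With all values distinct, the chi-squared test has no ability to detect a difference; that result needs only the group sizes. With rounded values it detects a 0.5 SD shift in somewhere between about 1% or fewer and about a third of trials, where the t test would detect it in about 94%. Those figures rest on the assumed SD, shift and rounding. The reversal itself does not.

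For the subjective global assessment the problem is a wrong and incompletely defined method, with little practical effect under 0/1 coding.

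The correction is editorial in kind, but it is needed because this is the only inferential rule the article states.

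**What to change.** Swap the order in the section 2.5 sentence, so that continuous variables are analysed by independent t tests and categorical variables by chi-squared tests. If a fuller protocol or analysis plan exists, check that it has the same pairing.

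The cost is one corrected sentence, with no change to data collection. Nothing further is needed to cure this error. In particular, it does not call for a baseline-adjusted model: section 2.4 mentions outcomes only after the intervention, and the article does not say that they are measured at baseline.

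### Eight unranked endpoints are each judged at P<.05 with no primary endpoint, so under no effect the chance of at least one significant difference is up to about one in three

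*Protocol article*

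**What the plan says.** Section 2.4 (Clinical endpoints) is a single sentence: "The clinical results are the biochemical parameters, anthropometry, as well as the subjective global assessment after intervention". It puts the three groups of outcomes side by side and calls none of them primary, secondary or exploratory.

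The Results section provides an empty table, titled "The clinical endpoints between the two groups", with one P-value column. Its ten rows hold:

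- three nutritional status categories (for example "Moderately malnourished"), which together are the SGA and form one categorical variable;
- four body and strength measures: BMI, triceps skinfold, arm muscle circumference and grip strength;
- three blood measures: haemoglobin, albumin and cholesterol.

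That is 1 + 4 + 3 = 8 endpoints.

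Section 2.5 (Statistical analysis) gives one threshold for all of them: "P* value <.05 indicates that there is statistical significance". The article has no multiplicity adjustment, no testing order and no exploratory label. The 100 patients per group in section 2.2 are not tied to any endpoint, so the sample size does not point to an implied primary either.

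**The concern.** A 5% threshold limits the false-positive rate of one test. When eight tests share that threshold and none is designated to carry the conclusion, the 5% no longer describes the trial as a whole. An ineffective nursing programme would have eight chances to produce a significant result, and the article gives no rule for weighing one significant marker against seven that are not.

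This matters for how the result will be used. The Conclusion section expects the work to help nurses build an evidence-based programme. A recommendation that rests on whichever of eight markers falls below .05 would not have the error rate that readers will assume.

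**Working it through.** **Inputs**

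- Threshold per test: 0.05 (section 2.5).
- Number of endpoints: 8 (Table 1, with SGA counted once).
- Group size: 100 and 100 (section 2.2).
- Sidedness: not stated. I assume two-sided tests, the usual default for the tests in section 2.5. I also take *t* tests to be meant for continuous variables and chi-squared tests for categorical ones.
- Correlation between endpoints: not given, so I vary it as an assumption.

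The article states no overall error rate, so there is no figure of its own to reproduce.

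**Chance of at least one significant difference, in either direction, under no effect**

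If the endpoints are independent: 1 − (1 − 0.05)^8 = 1 − 0.663 = 0.337.

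Nutritional markers in the same patients are likely to be positively correlated, which lowers this. Simulating eight null z statistics with a common correlation (300,000 runs each) gives:

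| Assumed correlation | Either direction | One direction only |
|---|---|---|
| 0 | 0.34 | 0.18 |
| 0.3 | 0.30 | 0.15 |
| 0.5 | 0.25 | 0.13 |
| 0.7 | 0.19 | 0.10 |
| 0.9 | 0.12 | 0.06 |

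A less uniform pattern (0.5 among the four body and strength measures, 0.4 between SGA and everything else, 0.2 otherwise) gives 0.29.

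**Only differences that favour the programme**

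A two-sided 5% test has a 2.5% chance of a false positive in a given direction. For eight independent endpoints: 1 − (1 − 0.025)^8 = 1 − 0.817 = 0.183. The ratio to a single test is 0.183 / 0.025 = 7.3, close to the either-direction ratio of 0.337 / 0.05 = 6.7. The directional figures are approximate, because a chi-squared test on three categories has no direction.

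**After the change**

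- One named primary endpoint: error rate 0.05 on that endpoint.
- Holm across eight: the smallest P value is compared with 0.05 / 8 = 0.00625, and the familywise error is at most 0.05 whatever the correlation.

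For a continuous endpoint with 100 per group and no dropout, the standardised difference detectable with 80% power is √(2/100) × (z for alpha + z for power):

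- alpha 0.05: 0.1414 × (1.960 + 0.842) = 0.396 SD
- alpha 0.00625: 0.1414 × (2.734 + 0.842) = 0.506 SD

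**The case against.** The best defence is that this is a condensed article. Multiplicity rules are normally written in an analysis plan, a fuller protocol may exist, and the registry record, which might name a primary endpoint, is not at hand. The threshold sentence is also conventional and would be correct for a primary endpoint. Part of this stands: the absence of an adjustment method alone would not be worth raising. But naming the primary endpoint belongs in the protocol. This article has an endpoint section, a statistics section and a ready-made results table, and together they fix an unranked set of tests under one threshold. A fuller plan that named a primary would have to be reconciled with all three.

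Some stronger readings are tempting and are not supported:

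- A reader might infer that the plan declares success if any one marker is significant. No section says so. Section 2.5 gives only a per-test threshold, and the fault is that nothing limits how the eight results are combined.
- A reader might take one in three as the error rate. It is an upper value that needs near-independence and counts differences favouring the control group as well.
- A reader might count ten tests, one per row, and obtain 1 − 0.95^10 = 0.40. The three SGA rows are mutually exclusive categories of one variable, so they cannot be independent, and the article does not say that each has its own test.
- A reader might argue that some markers have no clear favourable direction. The article specifies no direction for any marker, so I place no weight on this.

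**Conclusion.** The point holds. Followed as written, the plan leaves the trial's overall conclusion without a 5% error rate. For correlations from 0 to 0.5, the chance of at least one significant difference under no effect is about 25% to 34% in either direction, or five to seven times nominal. At 0.7 it is 19%. In the programme's favour alone it is about 18% under independence, against 2.5% for one test. Even at a correlation of 0.9 the either-direction figure is 12%, more than double nominal, so the conclusion does not depend on the correlation chosen.

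These sizes rest on counting SGA as one endpoint, on two-sided tests and on assumed correlations. The count of eight and the uniform threshold come from the article itself.

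**What to change.** Before enrolment, name in section 2.4 one primary endpoint that matches the aim of improving nutritional status, and state in section 2.5 that it alone is tested at 5% as the basis for the conclusion. The choice is the sponsor's. If SGA is considered, check it against section 2.1, which excludes patients on grounds that include malnutrition. That may leave little room for SGA categories to improve.

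For the other seven endpoints, either label them exploratory and report 95% confidence intervals, or put them under Holm (first step 0.05 / 7 = 0.0071). If Holm is chosen and error control is wanted over all eight, test the seven only when the primary is significant. Otherwise the two families together can reach 5% + 5% = 10%. If the sponsor prefers not to single out an endpoint, apply Holm across all eight.

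Report one P value for SGA, not one per category. In a simulation with an assumed 60/30/10 split, testing the three rows separately gave a 12% chance of at least one significant row.

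The cost is a few sentences in sections 2.4 and 2.5. A single primary loses no power on that endpoint. Holm across all eight raises the difference detectable with 80% power at its first step from about 0.40 to about 0.51 SD at 100 per group, and dropout would raise both figures.

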## Results

3

Table 1 indicates the clinical outcomes between 2 groups.

**Table 1 T1:** The clinical endpoints between the two groups.

Variables	Study group (n = 100)	Control group (n = 100)	*P* value
Well nourished			
Moderately malnourished			
Severely malnourished			
Body mass index			
Triceps skin-fold thickness			
Mid-arm muscle circumference			
Handgrip strength			
Hemoglobin			
Albumin			
Total cholesterol			

## Discussion

4

The technological innovations of PD have greatly decreased the complications related to treatment, so that patients can maintain PD for a long time.^[13,14]^ Nevertheless, patients with PD are characterized through the high risk of malnutrition, with the estimated prevalence of 40%.^[15,16]^ The former studies have suggested continuous follow-up plans and health care in CKD patients treated for PD, but have failed to focus on the management of nutrition.^[17]^ There is a lack of the tailored nutritional interventions for the patients and adequate monitoring by medical practitioners. This may lead to self-management of nutritional intake by patients and can cause confusion as they adjust to novel eating habits. In early 1970s, the OS is established, which contains 3 fundamental steps: problem, intervention, and result.^[18]^ Few researches have used the OS to deal with nutritional problems in patients with CKD receiving PD. Hence, its influences on improving the nutritional status of patients need to be in-depth investigated in clinical practice.

## Conclusion

5

This protocol can guide nurses to develop a nursing program based on evidence for patients with CKD receiving PD.
